## **6. Endpoints:**

### **Primary endpoint:**

The primary endpoint is based on the comparison of the increase of high-sensitivity troponin T plasma concentrations (measured with Roche hs-TropT assay; difference between post-implantation and pre-implantation concentrations) between patients receiving a passive fixation or an active fixation ventricular electrode.

### **Secondary endpoints:**

- Proportion of patients reaching a high-sensitivity troponin T level >0.014 ng/dl (formally acute coronary syndrome)
- High-sensitivity troponin T plasma concentrations level post-implantation in relation to procedure duration and fluoroscopy time, number of mapping sites during implantation, ejection fraction, serum-creatinine, single- or dual chamber pacemaker implantation, age, ischemic versus non-ischemic heart disease, and lead tip size
- Pacing and sensing performance of the ventricular leads after 3 months
- Lead-related morbidity (dislodgement, perforation) and mortality within three months

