Because the stimulation thresholds of active and passive fixation leads tend to be similar, and differences in the rate of lead dislodgement and perforation are marginal (trend towards superiority of active fixation leads in the first and passive fixation leads for the latter), the choice of an active or a passive ventricular fixation electrode is largely a matter of personal

preference of the implanting physician (4). This is especially true for the right ventricular apical lead position which encounters >90% of ventricular lead positions.

Bearing in mind the equal performance of both lead types, the ability to implant the electrode as atraumatic as possible has come into the focus for electrode selection. Transvenous insertion of either passive or active endocardial leads for permanent pacing is accompanied by troponin elevation compatible with myocardial damage, secondary to the direct myocardial trauma elicited by pacing leads. Published data mostly report troponin elevations within or very close to the range of “minimal myocardial damage” (6,7,8) but usually did not exceed 3 ng/ml (9). These cardiac troponin-I (CTN-I) elevations occurred within 6 h after implantation (6).

Although active fixation leads are thought to be potentially more traumatic and therefore may be correlated with a higher troponin release, no randomized trial has been conducted to evaluate myocardial micro-damage with respect to different electrode types.

Therefore the primary aim of the PACMAN trial is to investigate whether ventricular active or passive fixation electrodes are associated with a different amount of myocardial micro-damage which is reflected by potentially different levels of high-sensitivity troponin release after pacemaker implantation.

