### **5. Study procedure:**

After obtaining written informed consent to the pacemaker implantation and the study participation the baseline high-sensitivity troponin T plasma concentration will be determined. This will be done from a previously taken blood sample provided for standard clinical tests if the sample is not older than 24 hours. If no such sample is available or if retrospective analysis is not possible an additional blood sample is required. Prior to pacemaker implantation the patient will be randomly assigned to receive a CE-marketed, commercially available, ventricular passive or active fixation electrode. Randomisation will be stratified for single- and dual-chamber pacing and for centres in a 1:1 ratio between active fixation and passive fixation leads for right ventricular pacing; for atrial leads active fixation will be used. The randomisation will be performed in varying blocks for each of stratify and will be centrally generated in the Deutsche Herzzentrum München. The participating centres will be provided with sealed envelopes containing the randomisation information. During pacemaker

implantation all necessary – and clinically reasonable - efforts should be made to adhere to the randomised lead type. Cross-overs (to avoid unsuccessful pacemaker implantations) will be allowed on the basis of the individual judgement of the implanter. In case of cross-over, the primary endpoint will be evaluated on an intention-to-treat basis. After pacemaker implantation, the patient will be followed according to standard clinical practice. Standard clinical practice includes the drawing of blood samples post-implantation (usually the next morning). For study reasons this should be done between 6 and 24 hours after pacemaker implantation. On this occasion, additionally to the routine parameters, high-sensitivity troponin T plasma concentration will be determined. The patients will be followed for three months with respect to lead performance, necessity of lead revision and mortality.

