## **9. Statistics**

Because there is no data available on high-sensitivity troponin T release after pacemaker implantation, historic data from patients supplied with pacemakers in the German Heart Centre 2011 were used for sample size calculation. For this, data of the most recent 30 patients (most recent 15 patients with active fixation ventricular leads and most recent 15 patients with passive fixation ventricular leads) with available high-sensitivity troponin T levels before and after pacemaker implantation were analysed. They did not differ relevantly in their baseline

characteristics and the distribution of high-sensitivity troponin T plasma concentrations is shown in the following table.

[figure not shown]

A=active fixation; P=passive fixation;

delta.hsTroponin refers to change plasma concentrations measured in ng/ml

The distribution is non-normal and due to large variations in the values including negative increases of plasma concentration after pacemaker implantation a non-parametric test (Mann-Whitney U Test) is the most appropriate approach to sample size estimation.

Null hypothesis: The probability that a randomly selected patient of the study cohort who received an active fixation ventricular pacemaker electrode shows a larger increase of high-sensitivity troponin T after implantation than a randomly selected patient who received a passive fixation ventricular pacemaker lead is 50 %.  $H_0: P(A > P) = P(P > A) = 50\%$ .

In the cohort of historic patients from the German Heart Centre the above mentioned probability was  $P(A > P) = 59\%$ . For sample size calculation it was assumed that an effect of  $P(A > P) = 60\%$  or  $P(P > A) = 60\%$  would determine the least difference that would be considered as clinically relevant..

Assuming that there is a relevant difference between both groups, a total of 262 patients need to be recruited (131 patients per group) to find a significant effect with a probability (=power) of at least 80% on a two-sided level of significance of  $\alpha=5\%$  (10).

Assuming a drop-out rate of 10% for this acute study, a total of 290 patients (145 patients per group) will be enrolled in the study.

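### The first secondary endpoint sets its troponin T cut-off in ng/dl, while the protocol's own troponin T data are in ng/ml, so the cut-off as written is 100 times lower than the same figure in ng/ml

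*Protocol*

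**What the plan says.** The first item under Secondary endpoints in section 6 of the protocol reads "Proportion of patients reaching a high-sensitivity troponin T level >0.014 ng/dl". A bracketed label equates exceeding this level with a formal acute coronary syndrome.

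Two other places in the protocol attach a unit to a troponin value:

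- Section 9 (Statistics), in the note to the display of the historic patients: "delta.hsTroponin refers to change plasma concentrations measured in ng/ml". This is the same analyte as in the endpoint.
- Section 1 (Background), on published troponin elevations: "but usually did not exceed 3 ng/ml". The next sentence there names troponin I, so this is a different marker.

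The primary endpoint in section 6 names the assay and the contrast ("measured with Roche hs-TropT assay; difference between post-implantation and pre-implantation concentrations") but gives no reporting unit.

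**The concern.** The endpoint sorts patients into positive and negative, so the unit of the cut-off decides who is counted. The endpoint is in ng/dl and the protocol's only troponin T data are in ng/ml. Converting between the two is trivial, and the protocol need not spell it out. The difficulty is that a correct conversion gives a cut-off 100 times lower than the printed number would suggest to someone holding data in ng/ml.

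There are two ways to proceed, and neither is satisfactory. An analyst who converts correctly may get an endpoint that nearly every patient meets. An analyst who assumes a slip and applies 0.014 ng/ml reports an endpoint that differs from the protocol. The trial is multi-centre and international, so the question could also be settled differently in different places.

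**Working it through.** **Inputs from the protocol.** Cut-off 0.014 ng/dl (section 6, Secondary endpoints). Unit of the historic troponin T changes: ng/ml (section 9). Sample-size inputs: two-sided 5% level, 80% power, P(A>P) = 0.60 against 0.50, 1:1 allocation (sections 5 and 9).

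**Step 1. The protocol's own calculation, to see whether the cut-off enters it.** Noether's formula for the Mann-Whitney test with equal groups is

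N = (z₀.₉₇₅ + z₀.₈₀)² / [12 × 0.25 × (0.60 − 0.50)²] = 261.6, rounded up to 262.

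This reproduces the stated 262. Allowing for 10% drop-out, 262/0.9 = 291.1, within two patients of the stated 290. The troponin cut-off appears nowhere in this calculation.

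**Step 2. The unit conversion.** 1 dl = 100 ml, so 0.014 ng/dl = 0.014/100 = 0.00014 ng/ml. The ratio 0.014/0.00014 is 100.

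**Step 3. What the literal cut-off would do, under an assumption.** The protocol text gives no post-implant troponin T levels. The display in section 9 is not reproduced in the text available, and its note describes changes, not levels. The following range is therefore assumed: post-implant level X lognormal with median m from 0.001 to 0.05 ng/ml and log-SD s from 0.7 to 1.5. Then

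P(X > c) = 1 − Φ[(ln c − ln m)/s].

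For example, with m = 0.001, s = 1.5 and c = 0.00014: (ln 0.14)/1.5 = −1.31, and 1 − Φ(−1.31) = 0.905.

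| Median (ng/ml) | log-SD | Above 0.00014 ng/ml | Above 0.014 ng/ml |
|---|---|---|---|
| 0.001 | 0.7 | 99.75% | 0.01% |
| 0.001 | 1.5 | 90.5% | 3.9% |
| 0.003 | 1.5 | 97.9% | 15.2% |
| 0.010 | 1.0 | 100.0% | 36.8% |
| 0.014 | 1.0 | 100.0% | 50.0% |
| 0.030 | 1.0 | 100.0% | 77.7% |
| 0.050 | 0.7 | 100.0% | 96.6% |

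Over the whole assumed range, 90.5% to 100% exceed the literal cut-off, and at least 97.9% do so once the median is 0.003 ng/ml or more. For 0.014 ng/ml the range is 0.01% to 96.6%.

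**Step 4. Discrimination between arms.** Take one arm with median 0.010 and the other with median 0.014 ng/ml, both with log-SD 1.0. On these levels the probability that a patient from the second arm has the higher value is Φ[ln(1.4)/√2] = Φ(0.238) = 0.594. That is close to the 0.60 used for planning, although the planning figure refers to changes. At 0.014 ng/ml the arms differ by 50.0 − 36.8 = 13.2 percentage points. At 0.00014 ng/ml both are at 100.0% and the difference is nil to one decimal.

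**The case against.** The strongest reply is that this is a one-letter slip with an unlikely route to harm. An analyst who applies the printed 0.014 to data held in ng/ml never meets the low cut-off, and a result near 100% in both arms would be noticed. Concentrations are measured before and after implantation anyway, so the proportion above any cut-off can be recalculated without loss of data. No eligibility, stopping or treatment rule refers to 0.014. All of this stands, and it limits the severity. It does not remove the point, because the analyst who uses 0.014 ng/ml still departs from the written endpoint. A statistical analysis plan that silently used ng/ml would contradict the protocol.

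It can also be said that the background figure is weak support, since the sentence after it names troponin I. That is right. The point rests on section 9, which concerns the same analyte as the endpoint.

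A reader might infer that the protocol, as it stands, classifies almost every patient as positive. The documents do not support so flat a statement. They give no troponin T levels and no detection limit, and the proportions above come from an assumed distribution. A reader might also infer that the trial's main result is at risk. It is not: the primary comparison is planned as a rank test on changes, which does not depend on the unit, and neither the sample size nor the rule on the area under the ROC curve uses the cut-off.

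**Conclusion.** The inconsistency is established by the text alone: the endpoint's cut-off is in ng/dl, the protocol's own troponin T data are in ng/ml, and the two readings of 0.014 differ by a factor of 100.

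The consequence is conditional. If the cut-off is converted and applied literally, and if post-implant levels lie in the assumed lognormal range, about 90% to 100% of patients in both arms would exceed it, and the endpoint would tell the arms apart little or not at all. That 0.014 ng/ml is the intended figure is plausible but is not stated anywhere in the protocol.

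The effect is confined to one secondary endpoint. This should be fixed, but it does not threaten the primary analysis, the planned 262 evaluable and 290 enrolled patients, or the non-inferiority rule.

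**What to change.** Reconcile the first secondary endpoint in section 6 with section 9 so that troponin T carries one unit throughout the protocol. The sponsor should confirm the intended threshold from the assay's reporting unit and state it explicitly (0.014 ng/ml if that is the intended figure). The unit on the case report form and the constant in the analysis code should then be checked against the corrected text.

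The cost is one corrected unit and two checks. No new data are needed, and neither the sample size nor the primary analysis changes.

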### **Exclusion**

- Cardiac resynchronisation therapy or AAI pacing
- Revision (except for adding a ventricular lead to pre-existing leads)
- Temporary pacing
- ICD indication
- Right ventricular pacing aimed from the mid-septum, outflow tract or his bundle region
- Severe tricuspid regurgitation requiring active fixation leads
- Planned cardioversion during pacemaker implantation or within 24 hours thereafter
- NYHA IV
- (Cardiogenic) shock
- Heart Surgery, acute coronary syndrome, myocardial infarction, any revascularisation, cardioversion or ablation procedure within the last 4 weeks with elevated base line high-sensitivity troponin levels.
- Pulmonary embolism, stroke, dialysis within the last 4 weeks
- Patient not available for follow-up
- Patient's inability to consent or refusal to consent
- Age <18 years, pregnancy

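### As worded, the secondary troponin cut-off endpoint ignores baseline, so pre-existing elevation can be counted as procedural and the arm difference is diluted; a cheap fix is available

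*Protocol*

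**What the plan says.** Protocol section 6, under the secondary endpoints, lists the "Proportion of patients reaching a high-sensitivity troponin T level" above 0.014 ng/dl, and equates this with a formal acute coronary syndrome. The definition is an absolute level. It requires neither a rise nor a baseline value at or below the cut-off.

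Section 4 has one exclusion criterion that mentions troponin. It covers heart surgery, acute coronary syndrome, infarction and "any revascularisation, cardioversion or ablation procedure within the last 4 weeks with elevated base line high-sensitivity troponin levels". An elevated baseline alone, without one of those events, does not exclude.

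Section 5 provides the data needed to separate old from new elevation. Before implantation "the baseline high-sensitivity troponin T plasma concentration will be determined", and a second value follows: "For study reasons this should be done between 6 and 24 hours after pacemaker implantation". The primary endpoint in section 6 uses both, as the "difference between post-implantation and pre-implantation concentrations".

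**The concern.** The trial asks how much myocardial micro-damage implantation causes and whether lead type matters (section 1), and section 2 takes the increase in troponin as the marker of that damage. The cut-off endpoint measures something else: how many patients are above a level after the procedure, for whatever reason. A patient with the same elevated value before and after would count as an event and carry the protocol's acute coronary syndrome label, although nothing changed.

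Two things are at stake for this endpoint. The reported rate would overstate the procedural effect. And patients who are above the cut-off whichever lead they receive add equal numbers of events to both arms, which pulls the difference towards zero.

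**Working it through.** **The plan's own figures.** The protocol gives no calculation for this endpoint. Its sample size belongs to the primary endpoint and reproduces by Noether's formula: (1.96 + 0.8416)² / (12 × 0.25 × 0.10²) = 261.6, rounded up to 262, or 131 per arm. I use 131 per arm below, with the test "on a two-sided level of significance" of 5%.

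**Is a patient with an elevated baseline eligible?** Yes, unless another criterion applies. Section 4 ties the troponin condition to the listed events. That condition also shows that elevated baselines were foreseen. Section 9 adds that the historic data varied widely, "due to large variations in the values including negative increases of plasma concentration after pacemaker implantation". A fall requires a measurable level beforehand, but it does not show that the level lay above the cut-off.

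**Dilution.** Let f be the share above the cut-off at baseline who remain above it in either arm, and let p₁ and p₀ be the rates of new exceedance among the others.

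- Rate in an arm: f + (1 − f)p
- Difference between arms: (1 − f)(p₁ − p₀)
- Share of counted events that pre-existed: f divided by the mean of the two arm rates

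Neither f nor the rates are in the protocol. With assumed p₁ = 70% and p₀ = 50%:

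| f | Arm rates | Difference | Pre-existing share of events | Power, all patients (131 per arm) | Power, at-risk only (n per arm) |
|---|---|---|---|---|---|
| 0% | 70 / 50% | 20 points | 0% | 0.915 | 0.915 (131) |
| 20% | 76 / 60% | 16 points | 29% | 0.796 | 0.845 (105) |
| 40% | 82 / 70% | 12 points | 53% | 0.624 | 0.730 (79) |
| 60% | 88 / 80% | 8 points | 71% | 0.423 | 0.553 (52) |

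Worked line for f = 40%: 0.4 + 0.6 × 0.70 = 0.82; 0.4 + 0.6 × 0.50 = 0.70; difference 0.12; pre-existing share 0.4 / 0.76 = 0.53; at-risk n = 131 × 0.6 ≈ 79.

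Power is Φ{[|d| − 1.96√(2p̄(1 − p̄)/n)] / √[(p₁(1 − p₁) + p₀(1 − p₀))/n]}, with the rates, their difference d and their mean p̄ taken from the population analysed.

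Other assumed rates give the same direction. At f = 30%, 60% versus 40% gives 14 points and power 0.663 for all patients against 0.778 at-risk only. At the same f, 80% versus 65% gives 10.5 points and 0.578 against 0.625.

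**Does stratifying by baseline status help?** It depends on the measure. In this model the baseline-elevated stratum has 100% events in both arms.

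- Mantel-Haenszel risk difference: under 1:1 allocation the weights are proportional to stratum size, so the result is f × 0 + (1 − f)(p₁ − p₀). This is the same diluted figure.
- Mantel-Haenszel risk ratio: also unchanged. At f = 40% it is 0.82 / 0.70 = 1.17, against 0.70 / 0.50 = 1.40 among patients at risk.
- Mantel-Haenszel odds ratio: the all-event stratum adds zero to numerator and denominator, so it stays at (0.70/0.30) / (0.50/0.50) = 2.33. The crude odds ratio at f = 40% is (0.82/0.18) / (0.70/0.30) = 1.95. The Mantel-Haenszel test likewise takes nothing from that stratum.

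**The case against.** The case on the other side has five parts.

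- **No decision rests on this endpoint.** The superiority test, the sample size (section 9) and the non-inferiority rule all use the change in troponin. This stands. A reader might infer that the wording tilts the trial towards finding no difference between leads; the protocol does not support that, because the comparisons that answer its question are already corrected for baseline.
- **Randomisation balances baseline status in expectation.** This also stands. The fault is dilution and mislabelling, not bias between arms, and the proportion of all patients above a level is a legitimate descriptive quantity.
- **Reaching a level may mean newly crossing it, and a SAP could say so.** This is possible. But the protocol itself states the definition, and its words do not carry that restriction.
- **The size is unknown.** This stands. A reader might infer that a large part of the cohort starts above the cut-off; nothing in the protocol shows it. NYHA IV, shock, and recent dialysis, pulmonary embolism or stroke are excluded, which may lower f by an unknown amount.
- **Baseline-elevated patients may not stay above the cut-off.** Since some historic values fell, a patient slightly above could drop below. The factor (1 − f) is therefore an approximation.

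**Conclusion.** The point holds as a worthwhile, inexpensive improvement to one secondary endpoint. As worded, the endpoint can count pre-existing elevation as procedural, and it dilutes the arm difference by about (1 − f). The figures of 16, 12 and 8 points in place of 20 illustrate this under assumed rates and an assumed f; they do not estimate what this trial will show. They rest on baseline-elevated patients staying above the cut-off whichever lead they receive. The mislabelling does not depend on those figures: it arises for any patient who starts and stays above the cut-off. The primary endpoint and the non-inferiority assessment are not affected.

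**What to change.** Redefine the endpoint as the proportion of patients newly above the cut-off after implantation, among those at or below it at baseline. Report by arm the share already above it at baseline.

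If all patients are to be kept, use the Mantel-Haenszel odds ratio or test stratified by baseline status. A Mantel-Haenszel risk difference or risk ratio would not serve, since it leaves the dilution in place.

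The cost is a sentence or two in section 6 and no new measurement, because baseline troponin is already taken. The downside is a smaller sample for this comparison; in the scenarios above with f greater than zero, the restricted analysis still had the higher power.

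The same edit should settle the unit. The cut-off is given per dl in section 6, while section 9 reports troponin changes per ml, a 100-fold difference. The two must be reconciled before anyone can be classified as above or below at baseline.

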## **7. Study related risks:**

In both arms CE-marketed and commercially available electrodes will be used. There is no consensus which lead type (active or passive fixation) is the better one. Lead selection in clinical practise is based on personal preference of the implanter. As only centres experienced in the implantation of both lead types are accepted for the trial and circumstances which

require a specific fixation mechanism of the electrode are defined as exclusion criteria, there is no attributable risk to study participation of the patient and the randomisation procedure.

For study reasons additional laboratory analyses (high-sensitivity troponin T plasma concentration) will be performed. These analyses can - in the vast majority of cases - be made from samples that are drawn routinely. In few patients an additional drawing of blood (2 ml) will be required. The patient will not be charged for these additional analyses.

Data acquisition and handling is pseudo-anonymous and only the principle investigator of each contributing centre will be able to allocate acquired data to the name of the patient.

Thus, there is neither potential risk for the patients in participating in the study nor is there any benefit for the participating individual.

